## Abstract

**Introduction::**

With the rapid development of social economy, peoples dependence on computers and mobile phones is increasing day by day. This causes people to often overuse. Therefore, the incidence of Ocular muscle spasm has been increasing year by year in recent years. The disease usually starts and hides, which seriously affects the patients social image, daily life, and work.

**Methods/design::**

We will compare the clinical efficacy of thunder-fire moxibustion combined with acupressure with pure thunder-fire moxibustion on Ocular muscle spasm using random control method.

**Discussion::**

We aim to find a simple, safe, simple and effective Chinese medicine nursing technology that relieves Ocular muscle spasm.

**Trial registration::**

ClinicalTrials.gov,ChiCTR2000034187, Registered on 27 June 2020.

## Introduction

1

Ocular muscle spasm (OMS) refers to the involuntary beating of the muscles around the eyes. It can develop from pure upper or lower eyelid spasm to twitching of the upper and lower eyelids, and even to involuntary twitching of muscles on the same side.^[1]^ With the rapid development of social economy, peoples dependence on computers and mobile phones is increasing day by day. This causes people to often overuse. Therefore, the incidence of OMS has been increasing year by year in recent years.^[2,3]^ The disease usually starts and hides, which seriously affects the patients social image, daily life, and work. If it is not treated in time, it will gradually develop to other muscles of the face and even the convulsions of the mouth and mouth, and further develop into facial muscle spasm, which will cause great pain to the patient.^[4]^ At present, the etiology and pathogenesis of the disease are still unclear, and most of them start in adulthood. Bilateral onset is more common at the same time, about 20% of patients are unilateral onset. But as the disease progresses, both eyelids will be involved. The main treatment methods of OMS are drug sedation, acupuncture, and surgery.^[5]^ At present, there are many treatments for this disease, but it is only symptomatic treatment, which cannot effectively solve the essential problems of OMS patients. Oral drugs used to treat OMS in Western medicine often have large side effects and are relatively expensive.^[6]^ At the same time, Western medicine treatment is an invasive operation, increasing the infection rate. Acupuncture and moxibustion is one of the suitable techniques of Traditional Chinese medicine (TCM). Acupuncture has a unique effect on the treatment of this disease. According to the theory of internal organs and meridians of TCM, there is a certain organic connection between the physiological and pathological reactions of the human body and the corresponding acupoints. Stimulation (local compression, acupuncture, heating, acupuncture point closure, etc.) corresponding to acupuncture points can directly affect the patients physiological and pathological reaction process, which can lead to the occurrence or termination of physiological and pathological reactions.^[7]^Acupressure has the effect of warming meridians, while thunder-fire moxibustion has the functions of warming qi and blood, activating meridians and collaterals, which can effectively improve eye blood circulation and promote the normal state of the body.^[8]^ Thrunder-fire moxibustion combined with acupuncture point nursing technology can better relax the muscle tissue of the affected area, regulate nerves, improve local blood circulation, and promote metabolism. This method of operation is easy to operate, has little adverse reactions, a low chance of infection, and is easy for patients to accept. In addition, in the process of clinical treatment, patients should pay attention to rest, avoid excessive use of eyes, fatigue caused by long-term viewing of mobile phones, computers, etc., and avoid external mental stimulation. This study intends to compare the clinical efficacy of thunder-fire moxibustion combined with acupressure with simple thunder-fire moxibustion on OMS by using a randomized control method. Our aim is to explore the simple, safe, convenient, and effective TCM nursing technology to relieve OMS.

## Methods/design

2

### Study design and settings

2.1

This study will be a single-blinded, randomized controlled trial with 2 parallel groups. It will be conducted at Beijing Hospital of Traditional Chinese Medicine, Capital Medical University. This protocol was written and based on Standard Protocol Items: Recommendations for Interventional Trials guidelines. If they agree, they will sign an informed consent form. Only those participants who read and agree to the protocol and who sign the informed consent form will take part of the study, following the schedule described in Figure 1.

**Figure 1 F1:**
[figure not shown]
SPIRIT figure for the schedule of enrollment, interventions, and assessments. SPIRIT = Standard Protocol Items: Recommendations for Interventional Trials, TCM = Traditional Chinese medicine.

### Ethical aspects

2.2

This study will be approved by Beijing Hospital of Traditional Chinese Medicine Ethics Committee. It will be conducted in accordance with the protocol. The rules of confidentiality will be respected. The study protocols is funded through a protocol registry. The study is supported by the TCM evidence-based capacity building project.

### Participants

2.3

All the cases in this study originated from the ophthalmology clinic and ward of Beijing Hospital of Traditional Chinese Medicine. We will select 76 patients with clinically diagnosed ocular muscle spasm.

#### Diagnostic criteria

2.3.1

1.Early period is mostly intermittent convulsions of the orbicularis oculi muscles, which can reach other facial muscles on the same side;2.The degree of convulsions varies, which can be aggravated by factors such as fatigue, nervousness and conversation, and convulsions stop when falling asleep;3.There were no positive signs on the nervous system.

#### Inclusion criteria

2.3.2

This study will be conducted in China. We will enroll participants based on the following inclusion criteria:

1.meet the diagnostic criteria of OMS2.age 18 to 80 years old;3.have not used relevant therapeutic drugs or have been treated with other drugs, but have been discontinued for more than 2 weeks;4.with the consent of the patient Later, voluntarily join the research of this subject;

#### Exclusion criteria

2.3.3

Patients will be excluded if they meet the following criteria:

1.Patients with other neurological diseases;2.Those under the age of 18 or over 80, pregnant, or lactating women;3.Combined with patients with serious primary diseases such as heart, cerebrovascular, liver, kidney and hematopoietic system, mental illness;4.Patients with mental or legal disabilities;5.Suspect or indeed have a history of alcohol or drug abuse, or other diseases that reduce the possibility of enrollment or complicate enrollment according to the judgment of the investigator, such as frequent changes in the working environment, which are likely to cause loss of follow-up;6.Those who are known to be allergic to thunder-fire moxibustion components;7.Patients who are participating in clinical trials of other drugs;

One of the above is excluded.

#### Criteria for termination of trials

2.3.4

If the following happens, we will terminate the test. Severe acute disease response; severe allergic reactions and other adverse reactions; those who withdraw due to worsening or ineffective eye disease during treatment

### Interventions

2.4

Control group: Thunder-fire moxibustion. A course of treatment for 10 days, a total of 1 course. Specific operation steps: first turn the thunder-fire moxibustion on the patients forehead, reciprocate, moxibustion 2 to 3 cm from the forehead, and reciprocate left and right for 2 to 3 minutes, until the skin of the patients forehead is reddish; the patient closes his eyes and performs respectively on both eyes Rotate clockwise, the moxa stick is 1 to 2 cm from the acupoint, and each eye is about 2 to 3 minutes. Then moxa sticks from the far and near, respectively, to the points around the eyes of the eyes (*Taiyang, Yuyao, Sibai, Chengqi, Jingming, Cuanzhu apoint,* etc.). Stay for 1 to 2 minutes, and then move to the next acupoint. During the operation, it is necessary to pay attention to the reddish skin around the eyes of the patient. Avoid long time, otherwise it will cause dry eyes.

Intervention group: This group will be treated locally with thunder-fire moxibustion combined with acupressure. A course of treatment for 10 days, a total of 1 course. ① Operator: Having good communication skills after training in relevant professional knowledge. ② Acupoint pressing: *Jingming Point*: locate in the depression above the inner canthus. *Cuanzhu Point*: Located on the face, sunken brows. *Yuyao Point*: Positioned on the forehead with the pupil straight up. *Sizhukong Point*: Positioned at the depression of the brow tip. *Sibai Point*: It is located on the cheek, in the depression of the infraorbital hole. *Taiyang Point*: Locate between the brow tip and the outer canthus, about a depression pointing backwards. *Chengqi Point*: Located on the cheek, between the eyeball and the infraorbital margin. ③ Acupoint compression method: The operator presses with the thumb and abdomen, the direction is vertically downward, and the pressure is gradually increased from light to heavy. It is limited to the local sense of acid, numbness, swelling, heat and the patient can tolerate it. The operator should avoid sudden force application to prevent tissue damage. ④ Compression time: Press after moxibustion, 2 minutes per point. ⑤ Pressing time per point: 5 seconds, pause for 1 second. ⑥ Eye opening and closing state: eyes closed.

### Outcome measures

2.5

#### Primary outcome measures

2.5.1

We will formulate standards for evaluating the efficacy of OMS in accordance with the Standards for Diagnosis and Treatment of Traditional Chinese Medical Diseases. The specific evaluation criteria for the efficacy are as follows:

1.Cure: the twitching of the eye cells or facial muscles disappears without recurrence within half a year;2.Effective: the spasm level of the eye cells or facial muscles is reduced, the number of twitching is reduced, and the time between twitching is shortened;3.Ineffective: The degree of spasm of the ocular muscles has not improved. All patients were graded according to the degree of blepharospasm. Level 0 is without spasm. Level 1 is an increase in convulsions caused by external stimuli. Grade 2 is mild spasm, slight twitching of eyelids, and no dysfunction. Grade 3 is moderate spasm, with obvious eyelid spasm and mild dysfunction. Grade 4 is severe spasm, severe blepharospasm, obvious dysfunction, affecting work and life.

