### Sample size calculation

2.6

With reference to previous clinical trials on the application of thunder-fire moxibustion combined with acupressure in the treatment of OMS, the standard deviation was 3.13. The purpose of this trial was to observe the difference in relief of ocular muscle spasm between patients with conventional thunder-fire moxibustion and acupressure. We expect that the treatment group can cause 90% of the changes to be clinically meaningful, in line with the superior effect design of the measurement data, and the sample size formula of the measurement index is as follows: 

. Combined with clinical practice, α = 0.05, β = 0.2, and the table *f* (*α*, *β*) = 7.9 then the calculated sample size is 33 cases in each group. According to the 15% shedding rate, the sample size in each group is 38 cases, and the treatment group and the control group total 76 cases.

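### The primary-outcome category Effective asks for a shorter time between twitches, a sign of worsening that generally conflicts with the fewer twitches it also requires, so a typical improved patient fits no category

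*Protocol article*

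**What the plan says.** Section 2.5.1 (Primary outcome measures) introduces the scale with "The specific evaluation criteria for the efficacy are as follows" and gives three categories.

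- **Cure:** "the twitching of the eye cells or facial muscles disappears without recurrence within half a year".
- **Effective:** three conditions in one sentence. The first two are "the spasm level of the eye cells or facial muscles is reduced, the number of twitching is reduced". The third is joined to them by an 'and': "the number of twitching is reduced, and the time between twitching is shortened".
- **Ineffective:** "The degree of spasm of the ocular muscles has not improved".

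The same section also grades every patient from 0 (no spasm) to 4 (severe spasm). Nothing elsewhere in the article redefines the interval condition or gives it the opposite direction. Section 2.5.2 is a separate scale, based on percentage reduction in a syndrome score, and does not mention twitch intervals.

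**The concern.** The third condition points the wrong way. In a disorder of involuntary twitching, shorter gaps are a worse state than longer ones, yet the rule makes shorter gaps a requirement for counting as improved. It also sits beside a requirement for fewer twitches, which normally moves the gaps in the other direction.

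Effective is the category that separates partial response from no response. If its definition turns away the ordinary responder, the literal rule has nowhere to put that patient. If raters set the wording aside, the category depends on an unwritten judgement that can differ between raters and between patients. In both cases a reader of the results cannot tell what Effective meant.

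**Working it through.** No figure in the article bears on this point, so there is none to reproduce. The check is of direction first, then of coverage.

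**Step 1: direction.** Inputs are the second and third conditions of Effective in section 2.5.1. Let T be the observation time and n the number of twitches in it. Then mean interval ≈ T / n. The article states no observation window, so T = 60 minutes is an assumption for illustration only.

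| Twitches in 60 min | T / n | Counting gaps only, T / (n − 1) |
|---|---|---|
| 60 | 60/60 = 1.0 min | 60/59 = 1.02 min |
| 30 | 60/30 = 2.0 min | 60/29 = 2.07 min |
| 10 | 60/10 = 6.0 min | 60/9 = 6.67 min |

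Halving the count doubles the mean interval. The choice of T does not change the direction.

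**Step 2: the typical improved patient.** Take a patient with a lower grade, fewer twitches and longer gaps, and apply each definition.

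| Category | What it needs | Result |
|---|---|---|
| Cure | Twitching gone | Fails: twitching persists |
| Effective | Lower level, fewer twitches, shorter gaps | Fails on the third condition |
| Ineffective | Degree of spasm not improved | Fails: the degree has improved |

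No category fits.

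**Step 3: coverage in general.** Consider patients who still twitch, and read degree of spasm as the grade. The three conditions, each met or not, give 2 × 2 × 2 = 8 patterns.

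- Effective takes 1 (all three met).
- Ineffective takes 4 (grade not improved, whatever the other two do).
- The remaining 8 − 1 − 4 = 3 have a lower grade but miss at least one other condition, and belong nowhere.

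As written, the typical improved patient is one of those 3. Once the third condition is put in the direction of improvement, that patient moves into Effective. Three patterns remain uncovered, for example a lower grade with no fall in the twitch count. Correcting the direction therefore removes the main problem but does not make the scale exhaustive.

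**The case against.** **This is a translation slip.** Probably so. The English is visibly translated throughout, and the criteria are said to follow a Chinese standard that is not shown. Nothing proves that raters will work from the English phrase. However, the slip sits in the primary-outcome rule, and the intended meaning cannot be recovered from the article. A longer interval and a shorter duration of each episode are different measurements, and either could have been meant.

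**The two conditions do not exclude each other.** This stands. T / n describes a mean over a fixed window, and section 2.5.1 specifies neither a mean nor a window. Twitching is described as intermittent in section 2.3.1, so a patient could have fewer twitches packed into tighter clusters and meet both conditions. A reader might infer that Effective must be empty, and the documents do not support that. The condition still asks for a sign of worsening, and the clustered pattern is not the usual picture of improvement.

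**The effect on the primary comparison is uncertain.** This also stands in part. Section 2.6 sizes the trial on measurement data with a standard deviation of 3.13, section 2.8 compares efficacy between groups with t tests, and the 0 to 4 grade is untouched by the interval wording. The article nevertheless lists this scale as the efficacy criteria under its primary-outcome heading, and no text demotes it.

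**Bias from unblinded raters.** A reader might infer this, but the documents do not show it. Section 2.1 says only that the trial is single-blinded, without saying who is blinded, and section 2.7 keeps the randomisation envelopes away from those who treat or evaluate. The same wording applies to both arms, so neither a direction nor a size of bias can be derived. What remains is inconsistent classification, which does not depend on whether raters are blinded.

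**Conclusion.** The definition of Effective is wrong as written. It requires a sign of worsening, generally conflicts with another requirement in the same sentence, and leaves a typical improved patient without a category. This rests on two readings: that the 'and' joins all three conditions, and that the time between twitches means the gap from one twitch to the next. Both are the plain sense of the text.

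The number of patients affected cannot be derived from the protocol, which gives no expected rate of improvement without cure. It is tempting to assume that 40% to 60% of the 33 evaluable patients per group improve in this way, giving 0.40 × 33 = 13.2 to 0.60 × 33 = 19.8, or about 13 to 20. That only restates the assumption, and it also supposes that every such patient fails the third condition, which clustering need not allow. The defect does not depend on such a figure.

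**What to change.** 1. Check the source standard and restate the third condition in the intended direction of improvement: time between twitches lengthened, or duration of each twitching episode shortened, whichever the standard says.
2. Add one rule assigning patients who improve on some conditions but not all, so that the three categories cover everyone. One way is to let change in the 0 to 4 grade separate Effective from Ineffective in those mixed cases. The count and interval conditions need not be discarded; replacing the whole category with a one-grade drop would go further than the error requires.
3. Carry the same wording into the case report form and fix it before any patient is classified.

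The cost is a corrected phrase and one added sentence in section 2.5.1, with the matching form entry. The grade is already recorded for every patient, so no extra data are needed.

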### Statistical analysis

2.8

According to the m-ITT principle, all randomized cases will be included. And there is at least 1 treatment and 1 post-baseline data. The missing data are not filled, and the actual observation values are used for statistical analysis. The measurement data are described by mean, standard deviation, median, and quartile. If the data meets the normal distribution, it is compared with the baseline value at the time of enrollment, and a paired T test is used. Differences in efficacy between the 2 groups will be compared using independent sample *t* tests. If the normal distribution is not satisfied, a non-parametric test is used. The count data is described using a composition ratio. If the normal distribution is satisfied, the changes before and after treatment in the 2 groups are tested by X^2^. If the normal distribution is not satisfied, a non-parametric test is used. The statistical software is SPSS 24.0, when *P* < .05, it showed that the difference is statistically significant.

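### The primary-outcome category Effective asks for a shorter time between twitches, which contradicts the fewer twitches it also asks for and leaves most partial responders unclassified

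*Protocol article*

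**What the plan says.** Section 2.5.1 (Primary outcome measures) sets three levels of efficacy, said to follow a named standard for the diagnosis and treatment of Chinese medical diseases.

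- **Cure**: "the twitching of the eye cells or facial muscles disappears without recurrence within half a year".
- **Effective**: a lower spasm level, and then "the number of twitching is reduced, and the time between twitching is shortened".
- **Ineffective**: "The degree of spasm of the ocular muscles has not improved".

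The three parts of Effective form one list closed by *and*, so as printed all three are required. The same section adds a spasm grade from 0 to 4, which does not refer to intervals. Section 2.5.2 gives a separate classification by percentage fall in a syndrome score, and it does not use the interval either. No other section restates or corrects the interval condition.

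**The concern.** Two parts of Effective describe improvement: milder spasm and fewer twitches. The third, taken at its word, describes deterioration, because a shorter time between twitches is more frequent twitching. The second and third parts therefore pull against each other within one line.

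This is the middle level of the declared primary outcome. Treatment is a single 10-day course (section 2.4), and Cure requires twitching to stop and stay away for six months, so partial response is a natural result and the middle level is where it should be recorded. A rule that partial responders can hardly satisfy leaves raters to choose between applying it as printed, with patients who fit nowhere, and mending it privately, with a definition that may differ from rater to rater.

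**Working it through.** **No stated figure tests this point.** It concerns the logic of a definition. The sample size (33 per group, 38 after the 15% allowance) does not use these categories; section 2.6 sizes the trial on measurement data with a standard deviation of 3.13.

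**Step 1: direction.** In a fixed window of length T with N twitches, the mean time between twitches is about T / N. Section 2.5.1 gives no window, so the windows and counts here are assumptions.

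| Window | Twitches | Mean gap, T / N |
|---|---|---|
| 60 min | 30 | 60 / 30 = 2.0 min |
| 60 min | 15 | 60 / 15 = 4.0 min |
| 60 min | 10 | 60 / 10 = 6.0 min |
| 5 min (300 s) | 20 | 300 / 20 = 15 s |
| 5 min (300 s) | 10 | 300 / 10 = 30 s |

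Halving the count doubles the gap, whatever the window. Fewer twitches and a shorter mean gap are opposite movements.

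**Step 2: how often both hold by chance.** Counts and observed gaps vary from one observation to the next, so the two conditions can occasionally coincide. Twitching was simulated as a random (Poisson) process, before and after treatment.

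*60-minute window, 30 per hour before treatment, 20,000 patients per scenario:*

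| True rate after treatment | Fewer twitches | Fewer twitches and shorter mean gap |
|---|---|---|
| 24 per hour | 77.2% | 2.8% |
| 20 per hour | 91.2% | 1.9% |
| 15 per hour | 98.5% | 0.6% |
| 10 per hour | 99.9% | 0.2% |

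*5-minute window, 4 per minute before and 2 per minute after, 60,000 patients:* the count fell in 95.9%, the mean gap shortened in 5.0%, and both occurred in 2.1%.

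In the 60-minute runs, the larger the true benefit, the less likely the patient is to satisfy the pair.

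**Step 3: where the partial responder goes.** Take a patient with milder spasm, fewer twitches and longer gaps.

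- Cure: not met, because twitching persists.
- Effective: not met, because the gap has lengthened.
- Ineffective: not met, because the degree of spasm has improved.

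The three levels as printed do not cover this patient.

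**Step 4: what a repair would do.** If the third part reads as a longer interval, it agrees with the fall in count. If it reads as a shorter duration of each twitching episode, all three parts again point the same way. The two repairs measure different things, frequency and episode length, and nothing in the article chooses between them.

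**The case against.** The strongest reply is that this is a translation slip which no rater would apply literally. The article has other awkward English, the criteria are attributed to a Chinese standard that is not shown, and raters at the site may work from that text. The boundary between Effective and Ineffective can also be drawn from the degree of spasm alone, for which the same section supplies a 0 to 4 grade. Much of this stands: a slip is the likeliest explanation. It does not dispose of the point, because at least two repairs are plausible, they are not equivalent, and the printed rule belongs to the primary outcome.

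It is also fair to say that partial responders are not strictly barred. The contradiction is exact only for the mean gap over a fixed window. The diagnostic criteria (section 2.3.1) describe early disease as intermittent; if twitches come in bouts, gaps within a bout could shorten while the total falls. The simulations assume no such clustering.

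Three stronger readings are tempting, and the document does not support them.

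- *Worsening is counted as benefit.* A reader might infer this from the wrong sign. But the conditions are joined, so a patient who twitches more often fails the count condition and is not Effective. It could happen only if the interval were scored alone, which the text does not provide for.
- *Partial responders drop to Ineffective.* That level requires the degree of spasm not to have improved, and theirs has. They are unclassified.
- *A stated amount of power is lost.* The article gives no expected distribution over the three levels, so any power figure would rest on invented proportions.

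**Conclusion.** Wrong as written. The interval condition in Effective has the wrong sign and contradicts the count condition beside it, and no other part of the article corrects it. Read literally, a partial responder almost never qualifies: about 0.2% to 2.8% met both conditions across the scenarios tried, under assumed rates, assumed windows and random twitching. The direction of the contradiction does not depend on those assumptions; the percentages do. The practical harm is a gap in the primary outcome's categories, or, if raters mend the line themselves, the lack of one fixed definition. The sample size is untouched. Which wording was intended cannot be settled from the article.

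**What to change.** In section 2.5.1, before any patient is rated, check the third condition against the cited standard and make it point to improvement. Depending on what that standard says, either state that the time between twitches is lengthened, or state that the duration of each twitching episode is shortened. If the interval was meant, the condition may instead be deleted, because over a fixed observation time the twitch count already carries that information; if episode duration was meant, deletion would remove a separate feature. State also whether all three conditions are required for Effective, and put the same text in the case report form.

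The cost is one line in the protocol and one in the case report form, with no extra patients, visits or data.

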#### Efficacy evaluation

2.5.2

Refer to “Guidelines for Clinical Research of New Chinese Medicine”. Efficacy was evaluated by the ratio of the difference between the points before and after treatment compared to the points before treatment. Syndrome treatment efficiency = (total points before treatment total points after treatment)/total points before treatment × 100%.

1.Clinical control: clinical symptoms and signs disappeared or basically disappeared, and syndrome scores were reduced by ≥95%;2.Significant effect: clinical symptoms and signs were significantly improved, and syndrome scores were reduced by 70%;3.The signs and symptoms have improved, and the syndrome scores have decreased by ≥30%;4.Ineffective: the clinical symptoms and signs have not improved significantly, and the syndrome scores have decreased by less than 30%.

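### The primary outcome is not fixed to one variable, contrast and time point, and the sample size rests on a measure that fits neither candidate under the primary heading

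*Protocol article*

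**What the plan says.** All references are to the protocol article.

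- **2.5.1, Primary outcome measures.** A three-level rating is introduced with "The specific evaluation criteria for the efficacy are as follows": cure, effective, ineffective. Cure requires half a year without recurrence. The same paragraph goes on with "All patients were graded according to the degree of blepharospasm" and defines grades 0 to 4. The grade is given no time point, summary or between-group comparison. Nor does the section say which contrast of the rating decides.
- **2.5.2, Efficacy evaluation.** A further scale is described: "Efficacy was evaluated by the ratio of the difference between the points before and after treatment compared to the points before treatment". It is a percentage fall in syndrome score, cut into four bands, and is called neither primary nor secondary.
- **2.6, Sample size calculation.** The aim is worded as "The purpose of this trial was to observe the difference in relief of ocular muscle spasm". The calculation is for a continuous outcome, with "the standard deviation was 3.13" and "α = 0.05, β = 0.2, and the table *f* (*α*, *β*) = 7.9". The outcome that this SD describes is not named.
- **2.8, Statistical analysis.** "Differences in efficacy between the 2 groups will be compared using independent sample" t tests, with chi-square for count data and non-parametric tests as the fallback. No variable is named. One general threshold, P < .05, ends the section: "it showed that the difference is statistically significant".

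**The concern.** Efficacy is the word used for the rating in 2.5.1, for the syndrome-score scale in 2.5.2 and for the comparison in 2.8, so the text does not show which result decides the trial. The rating itself can be compared as a cure rate, as a total effective rate (cure plus effective) or as a full 2×3 table. The usual place to settle such a doubt is the sample size section, but its SD points away from both measures under the primary heading.

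Two things are at stake. If the deciding comparison can be picked after the data are seen, the planned 5% error rate no longer describes the superiority claim. And if the candidates disagree, the plan cannot say whether the trial succeeded.

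**Working it through.** **1. The plan's own figure.** Inputs from 2.6: α = 0.05, β = 0.2, f = 7.9, SD 3.13, 33 per group, 15% loss, 38 per group.

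- f = (1.960 + 0.842)² = 7.85 for a two-sided test, which matches 7.9. One-sided would be 6.18. The planned test is therefore two-sided.
- The difference δ cannot be read: the text gives no number for it and the formula was lost in extraction. With n = 2·f·SD²/δ², solving backwards gives δ = √(2 × 7.9 × 3.13² / 33) = 2.17, or 0.69 SD.
- 33 × 1.15 = 37.95, rounded up to 38, as stated.

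**2. Can SD 3.13 belong to a measure in 2.5.1?** The largest SD of a bounded score is half its range, apart from a small-sample factor.

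- Grade 0 to 4: 4/2 = 2.0.
- Rating scored 1 to 3: 2/2 = 1.0.
- Improvement in grade, if it runs from 0 to 4 levels, has the same limit of 2.0. An SD of 3.13 would need many patients worsening by several grades while many others improve by several.

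The back-solved δ of 2.17 also exceeds the whole range of a rating scored 1 to 3.

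**3. Error rate if any one of k measures may carry the claim.** Each is tested at two-sided 0.05. For independent tests the rate is 1 − 0.95^k: 1 − 0.9025 = 9.75% for k = 2 and 1 − 0.857 = 14.3% for k = 3. With a common correlation (assumed, since the document gives none), simulation of 2 million draws gives:

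| Correlation | 2 measures | 3 measures |
|---|---|---|
| 0 | 9.8% | 14.3% |
| 0.5 | 9.0% | 12.5% |
| 0.7 | 8.4% | 10.9% |
| 0.9 | 7.0% | 8.4% |

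These are 1.4 to 1.95 times 5% for two measures and 1.7 to 2.85 times for three.

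**4. The rating alone.** Simulation under no effect, 33 per arm, assumed shares of 30% cure, 50% effective and 20% ineffective, 200,000 runs, uncorrected chi-square. The cure rate, the total effective rate and the full table each reject in about 5%. At least one of the three rejects in about 10.5%.

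**5. Can the readings disagree?** Take 14/16/3 against 6/24/3 (cure/effective/ineffective, 33 per arm), an invented example. By uncorrected chi-square the cure rate gives P = 0.032, the full table P = 0.091 and the total effective rate P = 1.0. The conflict depends on the test: for the cure rate, Fisher's exact test gives 0.059 and the continuity-corrected chi-square 0.061, so no reading is then significant.

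**The case against.** The strongest reply is that 2.5.1 holds one measure. The effective and ineffective categories are defined by whether the spasm is less severe, and the grade follows directly, so it is naturally the tool for judging them. The syndrome score stands outside the primary heading and may be taken as secondary, and unadjusted secondary outcomes do not inflate the error of a primary claim. Section 2.8 gives a general threshold. It does not say that each measure is tested separately, or that one win is enough. A ranking may also stand in a full protocol or SAP that is not shown.

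Much of this stands. A reader might infer that the plan runs several confirmatory tests and that its error rate is two to three times 5%. The documents do not support that: the inflation is conditional on several measures being allowed to carry the claim, and 1.95 and 2.85 times are the ceilings for independent tests. These measures rate the same spasm or symptoms, so positive correlation and lower figures are likely.

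The reply does not remove the point. The document states neither the role of the grade nor the rank of the syndrome score. Even with one measure in 2.5.1, the contrast and time point remain open, and step 4 shows that this alone can about double the error rate. The mismatch with SD 3.13 is in the printed text and is not a matter of missing detail.

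**Conclusion.** The point holds as an under-specified primary outcome. No single variable, contrast and time point is fixed, and the sample size was calculated for a continuous measure that neither candidate in 2.5.1 can plausibly be.

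Its size is conditional. If more than one measure may support superiority at P < .05, the false-positive rate is about 7% to 10% for two measures and 8% to 14% for three, over assumed correlations of 0.9 to 0. If only the rating counts but its contrast stays open, the rate is about 10% to 11% under assumed shares of 30/50/20. If one contrast is fixed before analysis, it is 5%. The text does not show which case applies, and it should be settled before the data are seen. The limits on the SD need no assumption about correlation. They depend only on the scales as printed and, for the rating, on 1 to 3 scoring.

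**What to change.** In 2.5 and 2.8:

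1. Name one primary variable, one time point and one between-group test at two-sided 0.05. An example is the three-level rating analysed as a single ordered outcome, at a time point consistent with the half-year condition in its cure category.
2. State whether the 0 to 4 grade is an endpoint of its own or only the instrument for the rating.
3. Label all other measures, including the syndrome-score change, its bands and any collapsed cure or total effective rate, as secondary and supportive, reported with 95% confidence intervals. Claim superiority on the primary contrast only.

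In 2.6, state which measure the SD of 3.13 and the planned difference belong to. If that is not the named primary, restate the power that 33 evaluable patients per arm give for the primary.

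The cost is rewording before analysis, with no new data collection. There are two downsides: a significant secondary result alone would no longer support a superiority claim, and the restated power may be less favourable than 80%. Splitting α instead would be dearer. At the back-solved δ of 2.17 and SD 3.13, two measures at 0.025 each need 40 per group (48 after 15% loss, as n/0.85), and three at 0.0167 need 44 (52). With 33 per group, power per test would fall to about 72% and 66%.
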